## Abstract

**Background:**

Perioperative pain management is one of the most challenging issues for patients with spinal neoplasms. Inadequate postoperative analgesia usually leads to severe postsurgical pain, which could cause patients to suffer from many other related complications. Meanwhile, there is no appropriate analgesic strategy for patients with spinal neoplasms.

**Methods/design:**

This is a protocol for a randomized double-blind controlled trial to evaluate the effect of esketamine combined with pregabalin on postsurgical pain in spinal surgery. Patients aged 18 to 65 years scheduled for spinal neoplasm resection will be randomly allocated into the combined and control groups in a 1:1 ratio. In the combined group, esketamine will be given during the during the surgery procedure until 48-h postoperative period, and pregabalin will be taken from 2 h before the surgery to 2 weeks postoperatively. The control group will receive normal saline and placebo capsules at the same time points. Both groups received a background analgesic regimen by using patient-controlled intravenous analgesia (containing 100 μg sufentanil and 16 mg ondansetron) until 2 days after surgery. To ensure the accuracy and reliability of this trial, all the researchers and patients will be blinded until the completion of this study. The primary outcome will be the proportion of patients with acute moderate-to-severe postsurgical pain (visual analog scale, VAS ≥ 40, range: 0–100, with 0, no pain; 100, the worst pain) during the 48-h postoperative period. The secondary outcomes will include the maximal VAS scores (when the patients felt the most intense pain over the last 24 h before being interviewed) at 0–2 h, 2–24 h, 24–48 h, and 48–72 h after leaving the operating room and 24 h before discharge; the incidence of acute moderate-to-severe postsurgical pain at each other time point; chronic postsurgical pain assessment; neuropathic pain assessment; and the incidence of drug-related adverse events and other postoperative complications, such as postoperative delirium and postoperative nausea and vomiting (PONV).

**Discussion:**

The aim of this study was to evaluate the effect of esketamine combined with pregabalin on acute postsurgical pain in patients undergoing resection of spinal neoplasms. The safety of this perioperative pain management strategy will also be examined.

**Trial registration:**

ClinicalTrials.gov NCT05096468. Registered on October 27, 2021

**Supplementary Information:**

The online version contains supplementary material available at 10.1186/s13063-023-07178-3.

## Background

Pain is one of the most common complications for patients undergoing surgery. According to previous studies, almost 80% of patients undergoing spinal surgery suffer from acute postoperative pain [1], and over 60% of these patients might have persistent postoperative pain [2]. Poor perioperative pain management was an independent risk factor for persistent postoperative pain [3] and could increase the risk by 3 times [4]. Elderly patients with postoperative pain might have impaired cognitive function [5], which increases the risk of senile dementia [6]. Severe postoperative pain could also influence the emotional and mental health of patients [7, 8], which could be associated with unfavorable prognoses for the patients. Moreover, inadequate acute postsurgical pain management could result in longer hospitalization, decreased satisfaction, and higher hospital costs. Therefore, effective perioperative pain management, especially appropriate management of acute postoperative pain, is one of the most important links to help enhance the recovery of surgical patients.

One of the most challenging issues during the perioperative period is providing appropriate pain control measures to enhance the recovery of patients. Over the last decade, opioids have been the most commonly used drug in perioperative pain management strategies. However, the administration of opioids could be compounded by aspects of misuse, overdose, and addiction. Furthermore, clinical adverse events such as nausea and vomiting and respiratory depression have limited the use of opioids. In 2016, the American Society of Anesthesiologists (ASA) and American Society of Regional Anesthesia and Pain Medicine (ASRAPM) jointly published consensus guidelines for acute pain management. These guidelines indicate that ketamine [9] and pregabalin [10] can be used for the treatment of postsurgical pain.

The mechanisms underlying postsurgical pain might be peripheral and central sensitization because of nerve injury and inflammatory responses at the operative site. Previously, researchers have suggested that central pain sensitization might be related to N-methyl-d-aspartate (NMDA) receptor activation [11]. Ketamine, an NMDA receptor antagonist, reduces central pain sensitization by blocking the activity of NMDA receptors. A related meta-analysis found that intravenous ketamine could reduce VAS scores in the 24~48-h postoperative period and decrease opioid consumption [12]. S-Ketamine, one of the enantiomers of ketamine, is a more effective analgesic and has fewer side effects than ketamine. Regarding the effects of S-ketamine on acute postsurgical pain, a meta-analysis of 12 randomized controlled trials showed that intravenous S-ketamine could decrease the intensity of pain and opioid requirements only 24 h after surgery and may increase the incidence of psychotomimetic adverse events [13]. Unfortunately, the evidence level was only moderate or even low. Due to the differences in the S-ketamine intervention protocols and the types of surgery, more high-quality studies are needed.

At the same time, gabapentinoids (gabapentin and pregabalin) have gained more attention from researchers for their significant effect on neuralgia. These compounds can inhibit the modulation of neuronal excitability by blocking α2–δ subunits of presynaptic, voltage-dependent calcium channels, which are upregulated in central sensitization processes [11]. A meta-analysis of preoperative gabapentinoids for acute postoperative pain reported that gabapentinoids were associated with reduced pain scores and cumulative morphine consumption during the 48-h postoperative period [1]. In the same year, another meta-analysis showed the effectiveness of preoperative pregabalin on acute postsurgical pain [14]. In contrast, in 2020, a meta-analysis including 281 trials investigated the effect of perioperative gabapentinoids on postoperative acute pain and reported the noneffective analgesic effects of gabapentinoids in adult patients during the postoperative period [15].

Thus, we designed a randomized controlled study to explore the analgesic effects of a combination of esketamine and pregabalin after resection of spinal neoplasms to investigate whether the combined therapy could improve postoperative analgesia. The fundamental aim of this study was to find an effective and safe analgesic treatment to help patients undergoing spinal surgery and provide a new perspective regarding perioperative pain management strategies.

## Methods/design

### Study design

This study will be a single-center, randomized, double-blind, controlled trial with two parallel study arms. This equivalence trial aims to evaluate the analgesic effects of esketamine in combination with pregabalin after resection of spinal neoplasms. The enrolled subjects will be randomly allocated into the combined group (esketamine and pregabalin) and the control group (normal saline and placebo) in a 1:1 ratio. This study was approved by the Institutional Review Board of Beijing Tiantan Hospital, Capital Medical University, Beijing, China (KY-2021-081-02). This study (protocol version 1.4/date 2021.10.08) was registered on ClinicalTrials.gov on October 27, 2021 (NCT05096468). All participants or their legal representatives will provide written informed consent after screening and before randomization.

### Study setting and recruitment procedure

The recruitment of this trial will be conducted in Beijing Tiantan Hospital from 1 December 2021 to 31 August 2022, and the follow-up will be until 31 December 2022. Based on the electronic medical records of the hospital, potential participants will be individually screened after admission. Almost 100 patients underwent surgery in the spinal neurosurgery department at Beijing Tiantan Hospital in 1 month, and the proportion of patients with spinal neoplasms was nearly 60% in this population. The sample size is only 90 for our study. Therefore, the predicted 8-month duration of this study is enough to complete the recruitment. No extra measures will be taken to recruit a sufficient number. Participants meeting the eligibility criteria will be visited by the research staff to sign informed consent forms and provide baseline information. The flow chart of the study is shown in Fig. 1.

**Fig. 1 Fig1:**
[figure not shown]
Participant timeline showing the patient contacts in the study: enrolment, randomization, intervention, and follow-up

### Study population

Patients meeting the following inclusion criteria and not meeting the exclusion criteria at the time of randomization will be considered for enrollment.

#### Inclusion criteria:

Scheduled to undergo elective resection of spinal neoplasmsAge between 18 and 65 years oldASA I–IIISigned informed consent

#### Exclusion criteria:

Previous adverse reaction to ketamine, S-ketamine, or pregabalinA diagnosed history of severe chronic pain (defined as pain persisting at least 3 months before the surgery for any reason, with an NRS score greater than 6)Long-term medical history of analgesic treatment (gabapentin/opioids/ketamine)Aphasia or inability to cooperate with the pain assessmentsA diagnosed history of hepatic and renal dysfunctionA diagnosed history of psychiatric disorderThe patient was treated with gabapentin/pregabalin in the last 3 monthsDrug use disorderBody mass index > 35 kg/m^2^Pregnancy or lactation

### Randomization and blinding

Patients will be randomized 1 day before surgery using blocked, stratified randomization by independent research staff to 1 of 2 treatment groups (the combined group or the control group) after study enrollment. We will randomize the patients in a 1:1 ratio in blocks of four. The randomized allocation list will be generated by using a real-time, online system on the day before surgery. The randomization results will be maintained by independent researchers who will not participate in any other work of this study to guarantee allocation blinding. The presence of moderate or severe preoperative pain will be used as a basis for the stratification of patients (evaluated by a visual analog scale, range: 0–100, with 0, no pain; 100, the worst pain; moderate or severe preoperative pain is defined by a VAS score equal to or more than 40 mm).

Allocation concealment will be achieved using study capsules and intravenous infusions with identical appearance for placebo and drugs. All the trial drugs will be provided by a medicine company (Hengrui Induction, Jiangsu, China) with no other contribution to this trial. The appearance of all trial capsules (placebo capsules containing starch and pregabalin capsules) will be the same. Esketamine will be diluted to a concentration of 0.5 mg/ml with normal saline. Colorless 50-ml syringes containing clear esketamine or placebo (normal saline) solution will be prepared in a blinded manner by an independent research assistant. The randomization code will be marked on the syringes and the drug bottles of the study capsules. Only the study investigator who assigns participants to interventions will be unblinded to the treatment assignment. All other study researchers will be blinded to the treatment assignment, including responsible anesthesiologists and the neurosurgeons in charge of the patients, the outcome assessors, data analysts, and other relevant investigators.

### Intervention

In the combined group, the patients will be given both esketamine and pregabalin during the perioperative period. The patients will receive 2 capsules of pregabalin (75 mg/capsule, 150 mg total) 1~2 h before the surgery and 1 capsule twice daily during the 7-day postoperative period (75 mg/capsule, BID; 150 mg total; POD 1~7), followed by dose reduction to 1 capsule once daily for 7 days (75 mg/capsule, QD; 75 mg total; POD 8~14). At the same time, patients will be administered a bolus dose of 0.5 mg/kg esketamine after the induction of anesthesia and then receive continuous intravenous infusion at 0.12 mg/kg ·h (2 μg/kg ·min) during the 48-h postoperative period.

In the control group, the patients will be given the same number of placebo capsules as the combined group at the same time points (two placebo capsules 1~2 h preoperatively and twice daily postoperatively for 7 days, followed by a reduction to a single capsule once daily for 7 days), alongside a normal saline bolus after induction of anesthesia and intravenous saline infusion for the 48-h postoperative period.

### Perioperative anesthesia management

Perioperative anesthesia management will be standardized. After entering the operating room, the patients will be given standard electrocardiography monitoring. Anesthesia will be induced with propofol, sufentanil, and rocuronium/cisatracurium. Total intravenous anesthesia depends on target-controlled infusions and will be chosen to maintain anesthesia with propofol and sufentanil and keep the bispectral index between 40 and 60. Remifentanil will be prohibited in this study. For the potential impact on the evaluation of the operation, nerve block will not be considered. In addition, local wound infiltration (0.5% ropivacaine 20 ml) will be permitted before skin suturing if required by the surgeon. All the participants will be given the usual postoperative analgesia therapy by postoperative patient-controlled intravenous analgesia (PCIA, 0.5 ml per bolus (containing 0.5 μg sufentanil) with a lockout period of 15 min, 100 ml total), which will include 100 μg sufentanil and 16 mg ondansetron during the 2-day postoperative period. In the ward, all patients will receive parecoxib sodium (40 mg IV BID) or flurbiprofen axetil (50 mg IV BID) to receive the standard postoperative analgesic for at least 3 days. If the patients are experiencing moderate or severe pain (VAS score ≥ 40 mm), rescue analgesia will be given, including 0.5 μg sufentanil IV in the postanesthesia care unit (PACU) or 1 tablet Tylox (contained 325 mg acetaminophen and 5 mg oxycodone per tablet) in the ward. If the pain persists, the patients will receive 1 dose of 50 to 100 mg of intramuscular tramadol. All analgesic doses and names will be clearly recorded.

### Provisions for posttrial care

All of the participants will receive conventional postoperative care in the ward. The postoperative treatment will not be changed whether the patients enter the trial. The interventions of this trial are a combination of analgesic management added to the basic analgesic treatment, which will help the patients to get more comfortable feelings. The interventions are common drugs in the clinic, and the dosages are lower. Thus, the patients will be at low risk during the interventional period. Therefore, there is no anticipated harm or special posttrial care for the participants.

### Outcomes

The assessment of outcomes will be performed by two independent researchers. The results during hospitalization will be collected by the investigators through bedside interviews. The collection of postdischarge outcomes will be performed by telephone interview.

The primary outcome was the proportion of patients with acute moderate-to-severe postsurgical pain during the 48-h postoperative period (defined as a VAS score ≥ 40 mm). The schedule of enrollment, intervention, and assessments is presented in Fig. 2.

**Fig. 2 Fig2:**
[figure not shown]
Standard Protocol Items: Recommendations for Interventional Trials (SPIRIT) figure showing the schedule of enrollment, intervention, and assessments

Secondary outcomes include the following:Acute pain assessment: the maximal VAS score (when the patients felt the most intense pain over the last 24 h before being interviewed) 0–2 h, 2–24 h, 24–48 h, 48–72 h after leaving the operating room and 24 h before discharge; the incidence of acute moderate-to-severe postsurgical pain at each other time point (defined as the VAS score ≥ 40 mm)Subacute or chronic pain assessment: The incidence of postsurgical pain was assessed by a number rating scale (NRS: 0~10) at 1 month and 3 months (defined as an NRS score > 3)Neuropathic pain assessment: the short-form McGill pain questionnaire-2 (SF-MPQ-2) scores at 1 month and 3 months postoperativelyTotal opioid consumption within the 48 h period after surgeryEffective or noneffective button presses for PCIAQuality of anesthesia emergence evaluated by a 15-item quality of recovery scale (QoR-15) on POD3 and at dischargeThe incidence of psychotic side effects (such as hallucinations and dissociative symptoms) was determined using the Brief Psychiatric Rating Scale (BPRS) and Clinician-Administered Dissociative States Scale (CADSS) at 2 h after surgery, POD1, POD2, and POD3Adverse events included drug-related (palpitation, hypertension, dizziness, diplopia) and operation- or anesthesia-related complications, the incidence of PONV, and the incidence of postsurgical delirium at 2 h after surgery, POD1, POD2, and POD3Other outcomes: perioperative depressive/anxious symptoms assessed by the Patient Health Questionnaire 9 (PHQ-9) and Generalized Anxiety Disorder scale (GAD-7) on POD3, at discharge, and 1 month and 3 months after surgery

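### The 24-hour recall attached to every acute maximal VAS score contradicts the 0–2 h and 2–24 h windows, and may let preoperative pain into the primary outcome

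*Protocol article*

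**What the plan says.** The Outcomes section gives the primary outcome as follows: "The primary outcome was the proportion of patients with acute moderate-to-severe postsurgical pain during the 48-h postoperative period", with pain at this level meaning a VAS score of at least 40 mm. It does not say which VAS readings are used.

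The list of secondary outcomes, placed after Fig. 2, contains the only acute VAS schedule in the text. The maximal VAS score is explained as the time "when the patients felt the most intense pain over the last 24 h before being interviewed" and is assigned to "0–2 h, 2–24 h, 24–48 h, 48–72 h after leaving the operating room and 24 h before discharge". The abstract repeats both elements. No shorter recall is given for any window. The same list item adds "the incidence of acute moderate-to-severe postsurgical pain at each other time point (defined as the VAS score ≥ 40 mm".

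Under Randomization and blinding, "The presence of moderate or severe preoperative pain will be used as a basis for the stratification of patients", and "moderate or severe preoperative pain is defined by a VAS score equal to or more than 40 mm". The exclusion criteria remove severe preoperative pain only if it is chronic (at least 3 months, NRS above 6).

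**The concern.** A maximal score needs one observation period, and here two are given. The window label says the score covers, for example, the first 2 h after the operating room. The recall instruction says it covers the preceding 24 h. An interviewer who follows the instruction at 2 h invites the patient to report the worst pain of a day that was mostly before surgery.

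This matters because preoperative pain at the primary cut-off is expected in these patients, at least often enough to be the stratification factor. A patient with preoperative VAS of 40 mm or more could truthfully give that score at 2 h. The early secondary outcomes would then be mislabelled. If the same readings define the primary outcome, that patient becomes an event whatever the treatment did afterwards. A recalled maximum carries no time stamp, so the error could not be undone at analysis.

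**Working it through.** **1. Recall against window.** Time is counted from leaving the operating room. A 24-h recall at time t covers t − 24 h to t. Interviews are assumed to take place at the end of each window.

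| Interview | Window named | Period recalled | Match |
|---|---|---|---|
| 2 h | 0–2 h | −22 h to 2 h | No: includes surgery and, unless it lasted about 22 h, preoperative time |
| 24 h | 2–24 h | 0–24 h | No: repeats 0–2 h |
| 48 h | 24–48 h | 24–48 h | Yes |
| 72 h | 48–72 h | 48–72 h | Yes |

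An interview held before 24 h, inside the second window, would also reach back before the patient left the operating room.

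**2. Link to the primary outcome.** The secondary list speaks of VAS ≥ 40 mm at each 'other' time point, meaning other than those used for the primary outcome. No other acute VAS schedule appears in the text. The natural reading is that the primary outcome is any maximum of at least 40 mm over the first three windows, but the Outcomes section does not say so.

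**3. Which mismatch could reach the primary outcome.** The overlap at 24 h stays within 0–48 h, so it cannot change an any-event outcome over 48 h. Only recall of time before leaving the operating room can.

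**4. Illustration of size.** Inputs from Sample size calculation: 60% in the control group and 30% in the combined group, a difference of 30 points; 90 patients less 20% withdrawal leaves 90 × 0.8 / 2 = 36 per arm. Assumption, not in the document: a share q of patients in each arm is counted as an event on recalled preoperative pain alone, independently of postoperative pain. The observed rate is then q + (1 − q)p, and the difference is (1 − q) × 30 points.

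| q | Control | Combined | Difference | Power at 36 per arm |
|---|---|---|---|---|
| 0 | 60% | 30% | 30 points | 72.7% |
| 0.1 | 64% | 37% | 27 points | 62.4% |
| 0.2 | 68% | 44% | 24 points | 53.0% |
| 0.3 | 72% | 51% | 21 points | 45.4% |

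Power is by exact enumeration of the uncorrected two-sided chi-square test at 0.05. The 72.7% at q = 0 is already below the planned 80%. That belongs to the sample size and has nothing to do with recall, so only the change down the column is relevant here.

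The added events are q(1 − p). At q = 0.1 they are 0.1 × 0.4 = 4 points in the control group and 0.1 × 0.7 = 7 points in the combined group. The same recall error adds more events where fewer patients have true ones, so the difference shrinks by 3 points.

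**5. Without independence.** The points lost equal q times the true treatment difference among the patients so counted. The loss exceeds the table's if their benefit is above 30 points and is smaller if it is below. The Sample size section cites an incidence of nearly 80% among patients with preoperative pain, so independence is doubtful, but no treatment difference for such patients is given.

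**The case against.** The strongest reply is that the same sentence confines the scores to time after leaving the operating room, and that the primary outcome is called postsurgical and limited to the postoperative period. The parenthesis can be read as explaining 'maximal', that is, worst rather than current pain, and it fits the later windows and the pre-discharge assessment. The article also condenses a fuller protocol, and neither the case report form nor Fig. 2 is shown; either may word the question properly.

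Part of this stands. A reader might infer that the plan counts preoperative pain in its primary outcome. The documents do not support that: no rule says so, the maximal VAS is listed as secondary, and the stated windows point the other way. A reader might also take the power figures as the trial's expected loss. They are not, because the prevalence of preoperative VAS ≥ 40 mm is not given, nor is there any basis for how many patients would report it 2 h after leaving the operating room.

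What does not stand is that nothing needs correcting. The point concerns what the article states, not what it leaves out. It gives one explicit recall period, twice, and for two of the four postoperative windows that period disagrees with the window. It gives no rule for which prevails, and two researchers perform the assessments and could resolve it differently.

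**Conclusion.** The contradiction is established from the text alone. Followed literally, the recall rule makes the 0–2 h and 2–24 h maximal scores, and the incidences taken from them, cover periods other than those named.

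The effect on the primary outcome is conditional. It requires that the primary outcome uses this VAS series including the 0–2 h score (a strong inference), that interviewers apply the 24-h recall at 2 h, and that some patients report preoperative pain of at least 40 mm. In that case false events arise in both arms, and the difference shrinks as long as the treatment helps the patients concerned. The size cannot be computed from the document. Under independence, an assumed share of 10–30% cuts the 30-point difference to 27–21 points.

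**What to change.** Tie each question to its window. At 2 h, ask for the worst pain since leaving the operating room. At 24, 48 and 72 h, ask for the worst pain since the previous interview. Keep the 24-h recall only for the pre-discharge assessment.

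State in the Outcomes section that the primary event is any of the 0–2 h, 2–24 h or 24–48 h maxima of at least 40 mm.

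Do not add VAS readings taken when rescue analgesia is given to the primary event. That would change the endpoint, and the section on perioperative anesthesia management says only that analgesic names and doses are recorded, not the VAS value.

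The cost is a wording change to the case report form and interviewer script, with the matching protocol text. No visits are added and treatment is untouched.

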### Statistical analysis

Continuous data will be described as the mean with standard deviation (SD) or median with interquartile range (IQR) based on its distribution. The histogram and Kolmogorov–Smirnov tests will be used to evaluate the normality of the data distribution. Categorical variables will be summarized as counts and percentages. The primary outcome is categorical and will be analyzed by using the chi-square test or Fisher’s exact test. Regarding the secondary outcomes, based on the type of each variable, the difference between groups will be analyzed using *t* tests, Mann–Whitney *U* tests, and chi-square or Fisher’s exact tests as appropriate. We will use the modified intension-to-treat (mITT) analysis to report our results, and we will use per-protocol (PP) analysis to perform the sensitivity analysis. The methods for estimating effects and 95% CIs will be reported in our outcomes. Sensitivity analyses will be applied to determine the statistical nature of the missing data. A two-sided *P* value of 0.05 was considered statistically significant for the primary outcome. Because of the repeated measurement, the Holm–Bonferroni method will be used to adjust the *P* value for secondary outcomes. Statistical analysis will be implemented using SPSS version 23.0 software and Stata version 14.0.

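### The 1- and 3-month pain outcome (NRS > 3) is a prevalence that can include persisting preoperative pain, and its planned test ignores the preoperative-pain stratum

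*Protocol article*

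**What the plan says.** All places are in the protocol article.

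- **Outcomes, secondary outcomes list.** "The incidence of postsurgical pain was assessed by a number rating scale" (0 to 10), "at 1 month and 3 months (defined as an NRS score > 3"). No criterion for onset, site or change from before surgery is given.
- **Exclusion criteria.** Severe chronic pain is excluded, "defined as pain persisting at least 3 months before the surgery for any reason, with an NRS score greater than 6". Two further criteria exclude long-term analgesic treatment (gabapentin, opioids or ketamine) and gabapentin or pregabalin in the last 3 months.
- **Randomization and blinding.** "The presence of moderate or severe preoperative pain will be used as a basis for the stratification of patients", and "moderate or severe preoperative pain is defined by a VAS score equal to or more than 40 mm". Also: "We will randomize the patients in a 1:1 ratio in blocks of four".
- **Statistical analysis.** Secondary outcomes are compared with t tests, "Mann–Whitney *U* tests, and chi-square or Fisher’s exact tests as appropriate". Neither the stratum nor the preoperative score is mentioned in that section.

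**The concern.** The label and the case definition do not match. Incidence of postsurgical pain suggests pain that arises after, or because of, the operation. A score above 3 at a follow-up call is pain present at that time, whatever its origin. A patient with pain of 5 out of 10 before surgery and 5 out of 10 at 3 months meets the stated definition.

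Such patients can enter the trial. The pain-score exclusion removes only pain that has lasted at least 3 months and exceeds 6. Chronic pain of 4 to 6 passes it, and so does shorter-lasting pain of any level. The trial stratifies on preoperative VAS of at least 40 out of 100, roughly the level that later defines a case, so it expects patients of this kind.

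Two things are at stake. Readers may take the reported percentage as the rate of pain after surgery when part of it may be carried over. And the planned test leaves out a factor that the trial itself thought important enough to stratify on, in a comparison with at most 45 patients per arm.

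**Working it through.** **Inputs.** From the protocol article: 90 patients, 1:1, so 90/2 = 45 per arm before withdrawal; two-sided 5% level; case = NRS > 3. The article plans no rate for this outcome at 1 or 3 months, so there is no figure of its own to reproduce. Assumptions, for illustration only:

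- a share f of each arm, 0.20 or 0.40, has preoperative pain that stays above NRS 3 whatever the treatment;
- among the rest, new pain occurs in 30% (control) and 15% (combined).

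**Step 1: rates under two definitions in the same randomised patients.**

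Any pain above 3: rate = f + (1 − f) × p. New pain only: rate = (1 − f) × p.

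| f | Definition | Control | Combined | Difference | Risk ratio |
|---|---|---|---|---|---|
| 0.20 | any > 3 | 0.20 + 0.80 × 0.30 = 44% | 0.20 + 0.80 × 0.15 = 32% | 12 points | 32/44 = 0.73 |
| 0.20 | new only | 0.80 × 0.30 = 24% | 0.80 × 0.15 = 12% | 12 points | 0.50 |
| 0.40 | any > 3 | 0.40 + 0.60 × 0.30 = 58% | 0.40 + 0.60 × 0.15 = 49% | 9 points | 49/58 = 0.84 |
| 0.40 | new only | 0.60 × 0.30 = 18% | 0.60 × 0.15 = 9% | 9 points | 0.50 |

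Carried-over cases add the same f to both arms, so the risk difference is unchanged. The risk ratio moves towards 1.

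**Step 2: power of the unadjusted comparison, 45 per arm.** With d the difference and p̄ the mean of the two rates,

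power = Φ{[d√n − 1.96√(2p̄(1 − p̄))] / √(p1(1 − p1) + p2(1 − p2))}.

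- f = 0.20, any > 3: (0.805 − 1.96 × 0.686)/0.681 = −0.79, power 21%.
- f = 0.20, new only: (0.805 − 1.96 × 0.543)/0.537 = −0.48, power 31%.
- f = 0.40, any > 3: (0.604 − 1.96 × 0.705)/0.702 = −1.11, power 13%.
- f = 0.40, new only: (0.604 − 1.96 × 0.483)/0.479 = −0.72, power 24%.

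The numerator signal is the same within each pair. Only the variance differs: p1(1 − p1) + p2(1 − p2) is 0.464 against 0.288 at f = 0.20, and 0.494 against 0.230 at f = 0.40.

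**Step 3: the most that stratifying could recover.** Suppose the stratum with VAS of 40 or more were exactly the patients with persisting pain. Everyone in it would be a case in both arms, so it would carry no information. A stratified test would then rest on the other stratum, at 30% vs 15%:

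- f = 0.20: 0.80 × 45 = 36 per arm, power about 33%;
- f = 0.40: 0.60 × 45 = 27 per arm, (0.779 − 1.96 × 0.591)/0.581 = −0.65, power about 26%.

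This is a best case. If preoperative pain persists in only some of that stratum, the gain is smaller.

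**The case against.** **A reader might infer that the outcome dilutes the absolute treatment difference,** for example from 15 points to 12 or 9. The documents do not support this, and neither does the arithmetic. Fifteen points is the difference only among patients without persisting pain, which is another population. Among all randomised patients, new pain alone also differs by 12 or 9 points.

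**A reader might also infer bias between the arms.** Nothing supports that either. Allocation is random and stratified on preoperative pain, and the unadjusted test is valid.

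**The definition is read partly from silence.** The article is condensed, and the full protocol or the telephone script may ask about onset or site. This stands as a limit: the point is what the printed definition allows, not proof that such cases will be counted.

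**Lasting pain may be uncommon.** The two exclusions on previous analgesic use remove some of these patients, and removing the neoplasm may relieve pain. Stratifying on preoperative pain shows that current pain is expected, not that it will last 3 months. This also stands, and it means f could be small.

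**Persisting pain may respond to treatment.** The Background describes both drugs as acting on central sensitisation, so zero response is not a neutral assumption. With some response, the loss shown above would be smaller. The label would still be wrong.

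**Adjustment is often left to the analysis plan.** That is fair as a general rule. Here, however, the article does name the tests for secondary outcomes, and none of them uses the stratum.

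**Conclusion.** The point holds in a limited form. By its stated definition the outcome is the prevalence of pain above NRS 3 at 1 and 3 months, and it can include pain carried over from before surgery. The named test ignores the preoperative-pain stratum, which is already recorded for randomisation.

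The cost is in the relative effect and in precision, not in the absolute difference or in validity. Under the stated assumptions, power is about 21% instead of 31% at f = 0.20, and 13% instead of 24% at f = 0.40, while the risk ratio reads 0.73 or 0.84 instead of 0.50. The share with persisting pain, its lack of response to treatment and the new-pain rates are all assumed. Withdrawals and the Holm–Bonferroni adjustment, neither included here, would lower every power figure. Power is low under either definition in this illustration, so the correction makes the result clearer and somewhat more precise but does not rescue it. This is a minor point on a secondary outcome and does not touch the primary analysis.

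**What to change.** 1. Keep NRS > 3 at 1 and 3 months, and call the result the prevalence of pain above NRS 3.
2. Replace the unadjusted test for this outcome with an analysis stratified by the randomisation factor (preoperative VAS of 40 mm or more), for example Mantel-Haenszel, or one adjusted for the preoperative pain score. Report the risk difference with its 95% confidence interval alongside any ratio.
3. Optionally, report the proportion above NRS 3 separately in patients with and without preoperative VAS of 40 mm or more, as description only.

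A derived variable for pain that is new or worse than before surgery is less secure. The documented baseline score is a VAS from 0 to 100 and the follow-up score is an NRS from 0 to 10, so it would need a preoperative NRS or a mapping stated in advance.

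The cost is a change of wording and slightly more analysis work. No new visit, measurement, patient or change of eligibility is needed.
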